## Abstract

Spasticity in the upper limb is a common condition observed in individuals with Cerebral Palsy, post-stroke or following traumatic brain injury. Affected patients present with significant functional and care challenges. Advances in both conservative and surgical treatments necessitate improved assessment tools. This study aims to develop and validate an instrumented measurement procedure combining 3D motion analysis, surface electromyography (sEMG), and musculoskeletal modeling to assess wrist and finger spasticity and function. The goal is to create a preoperative assessment tool for surgical strategy determination and a postoperative outcome measurement. We hypothesize that this combination of technologies will offer superior assessment accuracy compared to traditional methods and provide predictive insights into therapeutical outcomes.

## Introduction

Spasticity is defined as a velocity-dependent increase in muscle stretch resistance [1], which is associated with increased muscle tone. Spasticity is one of the leading causes of impaired motor control and thus significant functional limitations in the upper limb, particularly in cases of Cerebral Palsy (CP), after traumatic brain injury, and following strokes. In the upper limb, the most common patterns include spasticity leading to shoulder adduction, shoulder internal rotation, elbow flexion, forearm pronation, wrist flexion and ulnar deviation, finger flexion, “thumb-in-palm” deformity, clenched fist, and swan-neck deformities of the fingers due to hyperactivity of the intrinsic muscles. If left untreated, spasticity can lead to muscle and later joint contractures, resulting in progressive functional loss of the upper limb and care problems.

The standardized clinical examination of patients with upper limb spasticity includes the assessment of muscle strength grades (MRC scale), as well as the assessment of muscle tone and the extent of spasticity using clinical scales (modified Ashworth Scale (MAS) [2] and Tardieu Scale (TS) [3]), and functional tests including video recordings (Leclercq 2003).

Conservative treatment methods include physiotherapy, occupational therapy, and splint therapy, possibly combined with oral antispastic medication or intrathecal administration of Baclofen®. After exhausting conservative therapy options, and depending on the level of suffering and the patient’s wishes, surgical therapy can be performed. This usually consists of a combination of tendon and nerve procedures. By means of intramuscular lengthening (fractional lengthening), release of the muscle aponeurosis, tendon lengthening (Z-lengthening), or possibly tenotomies, the overactivity of the spastic muscles is reduced, and optimally, the full range of motion of the adjacent joints is restored [4,5]. If this is not successful, additional arthrolysis or even arthrodesis may need to be considered. An essential second pillar of surgical therapy are the so-called hyperselective neurotomies (HSN), which are less commonly studied. In HSN, 2/3 of the nerve fibers innervating a particular muscle are severed to reduce or eliminate the spasticity of that muscle without loss of strength [6–8].

The advances in conservative and especially surgical treatment of spasticity, with the possibility of substantial reduction or elimination of spasticity, necessitate the further development of diagnostic capabilities. To best advise patients regarding optimal therapy, objective, standardized examinations and the collection of short- and long-term therapy results are essential. The scales used in clinical routine to assess spasticity (MAS and TS) are neither precise nor reliable [9] and cannot differentiate between the neural component of spasticity (spasticity) and the non-neural component (contracture).

With the advancement of 3D motion analysis, wireless wearable sensors, and new approaches from robotics and computer technology, various approaches to instrumented spasticity testing have been developed and summarized in a review [9]. To differentiate between spasticity and contracture, both mechanical variables such as joint angles, angular velocities, and joint moments, as well as electrophysiological parameters using surface EMG, should be collected [10,11]. These so-called integrated models often require a very elaborate experimental setup and are therefore not yet used in clinical routine [9]. However, it has been shown that instrumented spasticity testing using surface EMG and motion analysis is superior to MAS and TS [12].

In classical 3D motion analysis, infrared light-reflecting markers are placed on specific anatomical landmarks onto the skin, and their movement in space is captured using infrared cameras. Biomechanical models are then used to calculate joint angles for each instant of a movement. Various models are available for 3D motion analysis of the upper limb. The classical models of the upper limb capture shoulder, elbow, and wrist movements, while specialized hand models [13] capture all joints located distal to the wrist. The so-called U.L.E.M.A. model has already been successfully applied to analyze patients with CP in the upper limb [14].

Another promising approach for precise diagnosis and prediction of surgical outcomes is musculoskeletal modeling and simulation of movements and loads. Based on anatomical information from MRI images, cadaver studies, and 3D motion analysis [15,16], many generic models have already been created. From these generic models, an individual model for each person can be generated by combining body measurements with data from 3D motion analysis and surface EMG (sEMG). Such models mathematically represent the musculoskeletal structure of a specific individual, enabling the calculation of muscle forces, joint loads, muscle tendon lengths, and stretch velocities for specific movements that cannot be directly measured. This approach has already been successfully applied to patients with neurologically induced gait disorders (especially spasticity) [16]. However, there is currently no comparable modeling approach for the upper limb.

The goal of the proposed project is to establish, for the first time, a standardized, objective method for detecting wrist and finger spasticity in the upper limb to improve treatment decisions, conduct adequate outcome analyses, and, using additional musculoskeletal modeling, provide an instrument for predicting surgical outcomes.

## Hypotheses

The combination of 3D motion analysis and sEMG is suitable for objectively detecting spasticity in wrist and finger flexors, providing an effective preoperative assessment tool for surgical therapy strategy and postoperative outcome control.

To test the central hypothesis, the following sub-hypotheses will be investigated

a)Simultaneous recording of sEMG signals from all wrist flexors, extensors, and extrinsic finger extensors and flexors, as well as capturing all joint angles distal to the forearm using 3D motion analysis, is feasible in healthy participants and patients with spasticity.b)The combination of 3D motion analysis and sEMG measurement allows for a reliable measurement of wrist and finger spasticity.c)Objective detection of wrist and finger spasticity can be performed within a clinically acceptable timeframe.d)The proposed methodology is suitable for measuring postoperative improvement of wrist and finger spasticity after hyperselective neurectomy, tendon lengthening, and/ or transposition.e)A musculoskeletal modeling generated from 3D motion analysis can predict the postoperative outcome after surgical treatment for upper limb spasticity based on preoperative measurements.

## Materials and methods

This study uses a prospective, observational design to evaluate wrist and finger spasticity in healthy participants and patients undergoing surgical treatment for spasticity.

It is a monocentric study (BG Klinik Ludwigshafen, Ludwigshafen, Germany).

Participant recruitment began in February 2023 and is scheduled to conclude in January 2026.

### Ethical approval and trial registration

The study has been approved by the local ethics committee (2020–15528_2).

Clinical trial registration is provided (DRKS00035052).

### Participants

**Healthy Participants**: 20 arms of healthy participants will be recruited for baseline measurements.
**Inclusion criteria:**
No previous injuries of the upper extremityNo neurological impairmentsInformed consent**Patients**: Patients with upper limb spasticity will be recruited during consultations in a specialized outpatient clinic when presenting for evaluation regarding potential surgical intervention. Clinical assessments in the movement laboratory will be conducted preoperatively (and potentially a second time one week later), 6 months postoperatively, and 1 year postoperatively if surgery is performed. The approximate duration of each measurement is one hour.**Inclusion criteria**:Patients with spasticity of the upper extremity and an indication for surgery
**Exclusion criteria:**
Severe mental disability (inability to give consent)Botulinum toxin injection in the area of the upper extremity to be treated within the last 6 months

All participants provide written informed consent. If minors are included, written informed consent is obtained from parents or guardians.

Participant data will be stored in a pseudonymized form, ensuring that personal information is collected, shared, and maintained securely to protect confidentiality. Only the principal investigators have access to the key required to trace the pseudonymization, and this access is strictly regulated before, during, and after the trial.

### Equipment

**Surface EMG**: sEMG electrodes will be placed to capture muscle activity from wrist flexors (Flexor carpi ulnaris (FCU), Flexor carpi radialis (FCR)), wrist extensors (Extensor carpi radialis longus (ECRL), Extensor carpi radialis brevis (ECRB), Extensor carpi ulnaris (ECU)), extrinsic finger flexors (Flexor digitorum superficialis (FDS) 2–5, Flexor digitorum profundus (FDP) 2–5, extrinsic finger extensors (Extensor digitorum communis (EDC)), and extrinsic thumb flexor and extensor (Flexor pollicis longus (FPL), Extensor pollicis longus (EPL)). EMG signals will be normalized to maximum voluntary isometric contraction (MVIC) recorded at the beginning of the measurement session for each respective muscle group.**3D Motion Analysis**: Infrared light-reflecting markers will be placed on anatomical landmarks to capture joint angles using 3D motion analysis. Two hand marker sets [17–19] will be employed for detailed analysis of wrist and finger movements.

Target parameters are flexion/extension in the metacarpophalangeal joints (MCP) 1-5, flexion/extension in the interphalangeal joint (IP), flexion/extension in the proximal interphalangeal joints (PIP) 2-5, and distal interphalangeal joints (DIP) 2-5. The proposed hand models captures MCP 2-5 with 2 degrees of freedom (extension/flexion, abduction/adduction), IP, PIP, and DIP each with one degree of freedom (extension/flexion), and the thumb saddle joint (MCP 1) with 3 degrees of freedom (extension/flexion, abduction/adduction, rotation).

Using the U.L.E.M.A. model [14], wrist flexion and extension will be captured, modeling the wrist with three degrees of freedom (wrist flexion/extension, wrist radial/ulnar deviation, forearm pronation/supination).

The angular velocity is calculated as the first derivative of the joint angles recorded at each time point, and acceleration as the second derivative.

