**Fig 1 pone.0328528.g001:**
[figure not shown]
SPIRIT schedule: t1 = 7 days before t2; t2  = 1 day before surgery; t3 = 6 months after surgery; t4 = 1 year after surgery.

5**Outcome Parameters:** The following EMG parameters will be recorded for all specified muscles:▫**MVIC:** The highest EMG activity within a defined period of 250ms during maximum voluntary isometric muscle contraction.▫**EMG LV:** Average EMG activity during slow (30°/s) passive stretch within a defined period (starting 200ms prior reaching maximum stretching velocity until 90% of the maximal range of motion is achieved [12]).▫**EMG HV**: Average EMG activity during fast (180°/s) passive stretch within a defined period (starting 200ms prior reaching maximum stretching velocity until 90% of the maximal range of motion is achieved [12]).**EMGchange:** EMG HV - EMG LV [12].6

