### Sample size calculation

Based on our preliminary work, the following effect size and resulting sample size were calculated for the primary outcome parameter, EMGchange, during passive stretch of the biceps brachii in patients with elbow flexor spasticity (one-sided, α = 0.05, power (1–β) = 0.8) compared to healthy participants. (Table 1)

**Table 1 pone.0328528.t001:** Sample size calculation based on the primary outcome parameter (EMGchange (%MVIC)); SD = standard deviation.

Parameter	Mean (patient)	SD (patient)	Mean (healthy)	SD (healthy)	Effect Size	Sample Size per group
EMGchange	19.1	21.1	0.04	0.1	0.91	10

The sample size calculation for the pre-/post-surgical comparison is based on our preliminary data. In a group of 7 patients with elbow flexor spasticity who underwent hyperselective neurectomy (HSN) of the elbow flexors as a surgical treatment, we were able to perform objective spasticity testing of the elbow. For the primary outcome parameter, EMGchange, the following effect size and resulting sample size were determined (one-sided, α = 0.05, power (1-β) = 0.8) (Table 2):

**Table 2 pone.0328528.t002:** Sample size calculation for a pre-/post-analysis based on the primary outcome parameter (EMGchange (%MVIC)) in 7 patients with elbow flexor spasticity who underwent hyperselective neurectomy (HSN) of the elbow flexors; SD = standard deviation.

Parameter	Mean preop	SD preop	Mean postop	SD postop	Effect Size	Sample Size
EMGchange (n = 7)	21.7	23.7	7.4	4.2	0.65	16

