After analyzing the preoperative and 6 months postoperative measurements from a minimum of 15 patients, a first interim analysis will be conducted using a paired two-sample t-test to determine any significant changes in the defined outcome parameters (EMG LV, EMG HV, EMGchange, extension deficit for wrist flexors (FCR, FCU), and finger flexors (FPL, FDP, and FDS)). If normal distribution is not confirmed, the Wilcoxon test will be applied.

Upon completion of all postoperative measurements, changes in the defined outcome parameters (EMG LV, EMG HV, EMGchange, extension deficit for wrist flexors (FCR, FCU), and finger flexors (FPL, FDP, and FDS)) across the three measurements (preoperative, 6 months postoperative, 1 year postoperative) will be examined using one-way repeated measures ANOVA. If histogram analysis and the Kolmogorov-Smirnov test indicate that the data are not normally distributed, the Friedman test will be used as a non-parametric alternative to ANOVA for comparing the three measurements.

The significance level α is set at 0.05. For significant differences, a post hoc paired t-test will be conducted, with α adjusted for multiple testing using the Bonferroni-Holm correction.

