### Study limitations

There are some study limitations that have to be addressed and taken into account when interpreting the data. First there is no consensus on how to normalize EMG data in patients with spasticity. MVIC normalization is most commonly performed, although its well-known limitations in patients with reduced voluntary motor control. There exist no SENIAM guidelines for sEMG electrode placement on the forearm. The muscle bellies are very close together and partially overlap, suggesting significant cross-talk. As a result, it is unclear how reliably the sEMG data can be interpreted on the forearm. All electrode and marker placements will be documented with photographs. The recorded sEMG data will be visually inspected and assessed for potential cross-talk. The measurement effort for each individual patient is approximately 1 hour under the study protocol and needs to be minimized for implementation in clinical routine. Due to the low number of eligible patients, the study group will be heterogeneous and include individuals with CP post-stroke, and post-hemorrhagic spasticity. This has to be considered when interpreting data. Concerning the spasticity itself, there are no differences expected between patient groups. When evaluating upper limb function differences in learned and lost (post-stroke, post-hemorrhage) versus never learned (CP) movement patterns to due disturbed volitional motor control must be considered. At least for test-retest reliability in patients the additional effort for a second preoperative measurement might be too high and there might be not enough patients to be included for this special testing. On the other hand, spasticity is highly influenced by daily conditions, environment, emotional state, and temperature – raising the question of whether a test-retest measurement truly assesses the method itself or merely reflects fluctuations in the patient’s condition.

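### EMGchange is scaled to an MVIC taken in the session, surgery could alter that MVIC, and MVIC is not compared before and after surgery

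*Protocol article*

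**What the plan says.** - **Normalisation (Equipment).** "EMG signals will be normalized to maximum voluntary isometric contraction (MVIC) recorded at the beginning of the measurement session", separately by muscle group.
- **What MVIC is (Outcome Parameters, after Fig 1).** "The highest EMG activity within a defined period of 250ms during maximum voluntary isometric muscle contraction". It is an EMG amplitude, not a force, and it heads the list of EMG parameters recorded for every specified muscle. EMGchange is EMG HV minus EMG LV.
- **Unit of the primary outcome (Sample size calculation, Table 2 caption).** "Sample size calculation for a pre-/post-analysis based on the primary outcome parameter (EMGchange (%MVIC)) in 7 patients with elbow flexor spasticity".
- **Visits (Detailed work plan).** Patients have up to two preoperative sessions (t1, t2) and two postoperative ones (t3 at 6 months, t4 at 1 year).
- **What happens between them (Introduction; Hypotheses, item d).** The operations are hyperselective neurectomy (HSN), tendon lengthening and/or transposition. In HSN, "2/3 of the nerve fibers innervating a particular muscle are severed"; the same sentence says that strength is preserved.
- **Pre/post tests (Statistical analysis).** A paired test is planned "to determine any significant changes in the defined outcome parameters", followed by a three-visit repeated-measures analysis. Both lists contain EMG LV, EMG HV, EMGchange and extension deficit. Neither contains MVIC.
- **Disclosure (Study limitations).** There is no agreed way to normalise EMG in spasticity, and MVIC is used "although its well-known limitations in patients with reduced voluntary motor control".

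**The concern.** A %MVIC value is a quotient. If treatment acts on both parts, the quotient alone cannot show which part moved. Here the numerator is expected to fall because motor nerve supply to the muscle is reduced. Voluntary EMG in that muscle depends on the same nerve supply, and lengthening or transposition changes the conditions under which the muscle contracts. The denominator is therefore plausibly exposed to the treatment as well.

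Hypothesis (d), that the method can measure postoperative improvement, rests on this comparison. A fall in MVIC would hide part of a real reduction in stretch-evoked activity; a rise would add an apparent reduction. Three of the four listed outcomes are EMG measures that share this denominator. The one parameter that would reveal a shift is recorded but not placed in the comparison.

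**Working it through.** **1. The plan's own figure.** Inputs from Table 2: mean 21.7 before and 7.4 after surgery, effect size 0.65, N = 16, with one-sided α = 0.05 and power 0.8. The difference is 21.7 − 7.4 = 14.3, so the implied SD of differences is 14.3/0.65 = 22.0. A paired t-test at d = 0.65 needs 17 patients by the noncentral t and 15 by the normal approximation; power at 16 is 0.798. The stated 16 is reproduced within rounding. Sample size is not at issue here; this only fixes the scale of the outcome.

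**2. The algebra.** Let D be the unnormalised EMG HV − EMG LV and M the MVIC amplitude of the session.

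- EMGchange before = 100 × D_pre/M_pre
- EMGchange after = 100 × D_post/M_post
- With r = D_post/D_pre and k = M_post/M_pre: after/before = r/k

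The primary outcome shows only r/k. Without k, r (the change in stretch response) cannot be recovered.

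**3. Size if stretch EMG does not change (r = 1).** The postoperative value is 21.7/k. The document gives no value of k; those below are assumptions, applied as one common ratio for all patients.

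| Assumed k | 21.7/k | Apparent change |
|---|---|---|
| 0.5 | 43.4 | +100% |
| 0.8 | 27.1 | +25% |
| 0.9 | 24.1 | +11% |
| 1.0 | 21.7 | 0 |
| 1.1 | 19.7 | −9% |
| 1.25 | 17.4 | −20% |
| 1.5 | 14.5 | −33% |

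At k = 1.25 the apparent fall is 21.7 − 17.4 = 4.3 points, and 4.3/14.3 = 30% of the pilot difference. For the denominator alone to produce a fall from 21.7 to 7.4, k would have to be 21.7/7.4 = 2.93, so MVIC would have to almost triple.

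**4. What must not be computed.** Table 2's 7.4 comes from patients who had undergone HSN and is already in %MVIC. If the pilot normalised by session, any postoperative MVIC shift is already in it. The article does not say which MVIC the pilot used, so 7.4 should not be divided by a further k.

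**5. What cancels.** (HV/M)/(LV/M) = HV/LV, so the within-session ratio does not depend on MVIC. It is a different estimand: if surgery halves both HV and LV, EMGchange halves but the ratio stays the same.

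**The case against.** - **HSN is said to preserve strength.** This is the only statement in the document on voluntary output after surgery, and it leans against a large MVIC shift after HSN. It stands as a reason not to presume one. It does not close the point, because it concerns strength rather than EMG amplitude and does not cover the tendon procedures.
- **The limitation is already disclosed.** In part. The Study limitations name poor voluntary control in general, not a denominator that may change with treatment between visits.
- **Normalising within a session is there for a reason.** Electrodes are placed afresh months apart, on a forearm where the article itself notes overlapping muscles and no placement guideline. This stands, and is why the primary definition should be kept.
- **The shift is not wholly invisible.** Also right: MVIC is recorded, and extension deficit is a tested outcome that does not depend on it. But extension deficit is not the primary parameter and cannot show whether a change in EMGchange comes from its numerator.
- **Sensitivity analyses usually belong in the analysis plan.** Fair in general. Here, however, the article itself fixes the denominator and lists the pre/post outcomes.

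A reader might infer more than the document supports:

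- That the pilot effect would shrink to 7.4/(2/3) = 11.1 or 7.4/0.5 = 14.8 %MVIC if MVIC fell to two thirds or one half. This assumes that 7.4 was obtained at constant MVIC, which the article does not say; it may count the shift twice.
- That the test is prone to false positives. That needs a systematic rise in MVIC, for which the document offers no mechanism. Cutting nerve fibres suggests, if anything, a fall, which works against hypothesis (d).

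**Conclusion.** The point holds as an inexpensive improvement, not as an error that invalidates the comparison. The algebra is certain: a pre/post change in EMGchange mixes a change in stretch response with any change in MVIC, and the listed comparisons do not separate them. The amount is unknown. Under the assumed ratios of 0.8 and 1.25, with no change in stretch EMG, the apparent change is +25% and −20%.

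This rests on two readings: that the measurement session means each visit, which is natural but not stated word for word, and that surgery may alter voluntary EMG amplitude, which the document neither shows nor excludes. Nothing in the document shows that the bias is present, large, or in favour of surgery.

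**What to change.** 1. In Statistical analysis, add MVIC amplitude (unnormalised) to the parameters compared pre/post. Read any change against its t1–t2 test-retest variability, which reflects electrode re-placement. MVIC is listed among the outcome parameters, so the planned SEM and MDD can serve as the yardstick.
2. Add two supportive sensitivity analyses of the pre/post change: the unnormalised EMG HV − EMG LV, and the within-session EMG HV/EMG LV ratio, labelled as a different estimand.
3. Keep EMGchange in %MVIC as primary and impose no rule that the analyses must agree. The ratio and the %MVIC difference are on different scales, and both supportive measures have known weaknesses.
4. In Study limitations, state that a postoperative change in EMGchange may partly reflect a change in MVIC.

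**Cost.** Extra analysis of signals already recorded, with no new patients, visits or measurements. Unnormalised amplitudes are sensitive to electrode placement, and the ratio is unstable when EMG LV is near zero. The article also warns that too few patients may complete the second preoperative session, so the t1–t2 yardstick may be imprecise.
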